## **B. General Questionnaire Parents, version 02**

Onderstaande vragen hebben betrekking op algemene gegevens van u en uw kind. Er wordt aan u gevraagd uit één alternatief te kiezen en het bijbehorende antwoord aan te kruisen. Bij enkele andere vragen kunt u het antwoord achter de vraag schrijven.

### **Achtergrondgegevens moeder**

1. Werkt moeder (neemt deel aan arbeidsproces)?

- ☐ voltijd
- ☐ deeltijd
- ☐ niet
- ☐ niet van toepassing
- ☐ Anders, nl \_\_\_\_\_

2. Beroep moeder: \_\_\_\_\_

### **Achtergrond gegevens vader**

3. Werkt vader (neemt deel aan arbeidsproces)?

- ☐ voltijd
- ☐ deeltijd
- ☐ niet
- ☐ niet van toepassing
- ☐ Anders, nl \_\_\_\_\_

4. Beroep vader: \_\_\_\_\_

5. Welke taal wordt er thuis het meest gesproken?

- ☐ Nederlands
- ☐ Vlaams
- ☐ Frans
- ☐ Anders, nl \_\_\_\_\_

### **Achtergrondgegevens school**

6.

Naam: \_\_\_\_\_

Straat en huisnummer: \_\_\_\_\_

Plaats: \_\_\_\_\_

Telefoonnummer: \_\_\_\_\_

Voor- en achternaam leerkracht: \_\_\_\_\_

E-mail leerkracht (indien bekend): \_\_\_\_\_

7. Volgt uw kind speciaal onderwijs?

☐ ja      ☐ nee

8. In welke groep/leerjaar zit uw kind op dit moment?

Groep/leerjaar \_\_\_\_\_

9. Is uw kind ooit blijven zitten?

☐ ja      ☐ nee

10. Heeft uw kind een klas overgeslagen?

☐ ja      ☐ nee

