### **2.3 Secondary objectives**

The secondary objective of this research is to examine the effects of Healseeker on working memory and self efficacy. In addition, it is examined whether intervention effects vary as a function of gender, age, ethnicity, SES, intelligence level, comorbidity, game experience, severity of psychopathology and satisfaction. The distribution of these baseline characteristics should be taken into account when answering this additional question.

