### **4.2 Inclusion criteria**

Potential subjects (children and their parents) must satisfy all of the following criteria to be enrolled in the study:

1. All children included in the study will be from 8 to 12 years of age.
2. All children must have an official DSM-IV ADHD diagnose (all subtypes). The diagnosis will be assessed using the Kiddie-SADS Present and Lifetime version. Children with common diagnosed comorbid disorders (i.e. dyslexia, ODD) can participate in the study. Including children with comorbid disorders is both pragmatic because these comorbidities are very common among children with ADHD, and clinically relevant because the included children will be representative of the clinical population.
3. All children need to be stable on ADHD treatment, both pharmacological and psychological, for at least two months prior to start of the intervention. Stable treatment can also include no pharmacological and psychological treatment. Participants must, when possible, continue this treatment throughout the intervention period and between measurement moments. All types of treatments, both pharmacological and psychological are accepted. Whether a child is on stable treatment will be assessed by interviewing parents, who have the best overview of children's treatment and actual use of treatment.
4. Minimum total intelligence score must be 80. If the total intelligence score is not known, has been established by a non-COTAN approved test or has been performed more than two years previous to the start of the intervention, total intelligence score will be established using two subtests of the Wechsler Intelligence Scale for Children third version (WISC-III-NL; Wechsler, 2005).
5. Children can only be included after a written informed consent has been signed by both parents or legal guardians. It is important that parents understand the information and are able to fill out the consent form. Twelve year olds have to give their own written informed consent in addition to their parents/legal guardians.
6. Both children and at least one of the parents/legal guardians must have a reasonable understanding of the Dutch language in order to understand the messages in the game, and have clear communication with the researchers.

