## 8. STATISTICAL ANALYSES

The modified ITT analysis set will include all randomized subjects who have both a baseline and at least one post-baseline efficacy assessment. Hochberg procedure (Biometrika, 1988) will be used to control the experiment-wise alpha level at 0.05 for the multiple primary endpoint analyses. All tests will be two-sided.

For all outcome measures descriptive statistics (mean, SD, median and range) as well as their changes from T0 (Baseline) will be calculated by treatment group. Within-group comparisons of changes at T1 (Week 10) from T0 will be conducted in both groups.

To assess whether effects are maintained after stopping the game, within-group comparisons of changes at T2 (Week 20) versus T1 will be performed in the Immediate group. To assess effects of game after waiting period, within-group comparison of changes at T2 versus T1 will be conducted in the delayed group.

An analysis of covariance (ANCOVA) model that includes treatment, site and gender as factors and baseline as covariate, will be used for the primary outcome measures to estimate the difference between the two groups in changes from T0 at T1.

Exploratory analyses may be conducted as deemed appropriate to examine whether intervention effects vary as function of demographic and baseline characteristics (e.g. age, gaming experience), to explore correlations between different measures, to investigate potential mediating effects (e.g. working memory, self-efficacy).

All adverse events will be listed. Special attention will be given to those subjects who discontinued due to an adverse event.

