| 38 | Heeft opzettelijk brand gesticht met de bedoeling ernstige schade aan te richten                                                                                                                                    |  |  |  |  |
| 39 | Heeft vaak moeite met het organiseren van taken en activiteiten                                                                                                                                                     |  |  |  |  |
| 40 | Heeft ingebroken in andermans huis, gebouw of auto                                                                                                                                                                  |  |  |  |  |
| 41 | Is vaak vergeetachtig bij dagelijkse bezigheden                                                                                                                                                                     |  |  |  |  |
| 42 | Heeft een wapen gebruikt dat anderen ernstig lichamelijk letsel kan toebrengen (bijvoorbeeld: een knuppel, steen, gebroken fles, mes, vuurwapen)                                                                    |  |  |  |  |

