| 9. Begint pas op het laatste moment aan opdrachten of karweitjes                                                                               |  |  |  |
| 10. Denkt niet vooruit bij huiswerkopdrachten (als uw kind nooit huiswerk heeft, kruis hier het vakje "nooit" aan)                             |  |  |  |
| 11. Geschreven werk ziet er slordig uit                                                                                                        |  |  |  |
| 12. Heeft moeite dingen te doen die nodig zijn om doelen te bereiken (geld sparen voor iets speciaals, leren voor een goed cijfer)             |  |  |  |

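### The primary ANCOVA leaves out age and T0 symptom severity, both already collected; prespecifying them would give a small, nearly free gain in precision

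*Protocol*

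**What the plan says.** Protocol section 8 specifies, for the three primary outcomes, "An analysis of covariance (ANCOVA) model that includes treatment, site and gender as factors and baseline as covariate", used "to estimate the difference between the two groups in changes from T0 at T1". Site and gender are also the two stratification factors (section 6.2).

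Age and severity appear elsewhere, but not in this model:

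- **Age.** Section 4.2 states: "All children included in the study will be from 8 to 12 years of age". Age is therefore known for every child. Attachment B also asks for the school year: "In welke groep/leerjaar zit uw kind op dit moment".
- **Severity.** Table 1 schedules the parent VvGK once, at T0, for all children.
- **Planned use.** Section 2.3 says "it is examined whether intervention effects vary as a function of gender, age, ethnicity, SES" and lists severity further on. Section 8 allows exploratory analyses to "examine whether intervention effects vary as function of demographic and baseline characteristics (e.g. age, gaming experience". Both passages concern effect modification, not adjustment of the primary comparison.

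Section 6.1.3 defines the primary outcomes as parent total scores: BRIEF plan/organise, the self-constructed time-management scale and SSIS cooperation. It mentions no age-normed score.

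**The concern.** The outcomes are rated in children of 8 to 12, and several items plausibly shift with age or school stage. Attachment D asks about homework planning, long-term projects and unaided routines. In Attachment C some items tell the parent to tick the most favourable answer when the child has no homework, for example "Denkt niet vooruit bij huiswerkopdrachten (als uw kind nooit huiswerk heeft, kruis hier het vakje 'nooit' aan". The VvGK contains an item close to the planning outcome: "Heeft vaak moeite met het organiseren van taken en activiteiten".

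A single T0 score carries measurement error; section 6.1.2 reports an alpha of 0.85 for the time-management scale. Age and a second T0 rating may therefore predict part of the T1 score that the T0 score misses. What they would predict stays in the error term of the primary tests. Precision is at stake, not validity.

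**Working it through.** **Inputs from the protocol (section 4.5):** difference 8 points, SD of change 16, 78 evaluable per group, two-sided 5%, stated power 87%. Hochberg over three endpoints makes 0.05/3 the strictest step.

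**Inputs assumed:** the T0-T1 correlation ρ, equal variances at T0 and T1, and the share R² of residual variance that the added covariates remove. None of these is in the documents.

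**Step 1. The plan's own figure.** The noncentrality is 8 / (16 × √(2/78)) = 3.12. The noncentral t gives 87.3% at 5%, which reproduces the stated 87%, and 75.8% at 0.05/3.

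**Step 2. What the planned baseline covariate already gives.** Section 4.5 describes 16 as the SD of change from baseline, not as the ANCOVA residual SD. Under equal variances the residual SD is 16 × √[(1 − ρ²) / (2(1 − ρ))] = 16 × √[(1 + ρ)/2]. That is 13.86, 14.31 and 14.75 for ρ = 0.5, 0.6 and 0.7. The comparison should start from these values.

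**Step 3. Adding covariates.** Multiply the residual SD by √(1 − R²). The factor is 0.990 for R² = 0.02, 0.975 for 0.05 and 0.959 for 0.08, so the standard error falls by 1.0%, 2.5% and 4.1%. Power by noncentral t, 78 per group, with two further degrees of freedom spent (site and gender degrees of freedom ignored):

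| ρ | level | planned model | R² = 0.02 | R² = 0.05 | R² = 0.08 | largest gain |
|---|---|---|---|---|---|---|
| 0.5 | 0.05 | 94.8% | 95.1% | 95.7% | 96.2% | 1.4 points |
| 0.6 | 0.05 | 93.4% | 93.9% | 94.5% | 95.1% | 1.7 points |
| 0.7 | 0.05 | 92.0% | 92.5% | 93.2% | 93.9% | 1.9 points |
| 0.5 | 0.05/3 | 88.1% | 88.8% | 89.8% | 90.8% | 2.8 points |
| 0.6 | 0.05/3 | 85.6% | 86.4% | 87.6% | 88.7% | 3.1 points |
| 0.7 | 0.05/3 | 83.2% | 84.0% | 85.3% | 86.5% | 3.3 points |

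With R² = 0 nothing is gained. The same figures apply to the other two outcomes only if the effect size of 0.5 in section 4.5 is on the same basis (8/16 = 0.5).

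**Step 4. Is 0-8% a reasonable range?** For one covariate, the partial correlation with T1 given T0 is (r_x1 − ρ·r_x0) / √[(1 − ρ²)(1 − r_x0²)], where r_x0 and r_x1 are its correlations with T0 and T1.

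- *Lower end.* With ρ = 0.5, r_x0 = 0.6 and r_x1 = 0.3, the numerator is 0.3 − 0.5 × 0.6 = 0. A prognostic covariate can add nothing.
- *Moderate case.* Let age correlate 0.2 and severity 0.4 with both scores, and let the two be uncorrelated. R² is then 0.083, 0.063 and 0.044 for ρ = 0.5, 0.6 and 0.7.
- *Age alone at 0.2.* R² is 0.014, 0.010 and 0.007. From the planned-model power in step 2 this adds about 0.2-0.3 points at 5% and 0.3-0.5 at 0.05/3.

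**The case against.** The strongest reply is that this is a preference. The model contains both stratification factors and the outcome's own T0 value, randomisation protects the estimate, and the power statement holds without further covariates. All of that stands.

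A reader might infer more than the documents support:

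- *That the omission biases the comparison, or that a chance age imbalance invalidates it.* Chance imbalance is allowed for in the type I error, and much of any age effect is already carried by the T0 score.
- *That a substantial gain is being forgone.* Raw dependence of the totals on age or severity is not enough; only what they predict beyond the T0 score counts. Stronger correlations (0.3 for age, 0.5 for severity) would give R² of about 9-17% at ρ = 0.7-0.5, but nothing in the documents supports them. Starting from 87% power also overlooks the baseline adjustment already planned.
- *That all three outcomes would benefit alike.* The VvGK overlap is with planning. No comparable overlap with SSIS cooperation is shown, and section 6.1.1 gives no key assigning VvGK items to domains.

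The VvGK also carries a condition. Table 1 places it in the column for T0 measurements after randomisation. Footnote c places it before randomisation, and section 6.2 puts collection of baseline data before randomisation. The parents who complete it know the allocation once it is made, so a rating given afterwards could be affected by it.

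**Conclusion.** The point holds as an optional refinement. Section 8 fixes a valid model that omits two variables already collected. Including them would probably improve precision slightly and would cost almost nothing.

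The size rests on R² of 0-8%, ρ of 0.5-0.7, equal T0 and T1 variances and 16 being the SD of raw change. On that basis the gain is at most about 2 power points at 5% and about 3 at the strictest Hochberg step, and it may be nil. Most of it would have to come from the VvGK rather than from age. The school-year item only supports the idea that school stage matters. It is not the variable to add, because it invites two differently named grade measures from two countries.

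**What to change.** Before data are seen, extend the primary ANCOVA in section 8 to: treatment, site and gender as factors; the T0 value of the outcome, age at T0 (continuous) and the T0 VvGK attention-deficit score as covariates.

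First reconcile the Table 1 column heading with footnote c and section 6.2, so that the VvGK is confirmed as completed before allocation. If that cannot be confirmed, add age only and accept that the gain is then probably below half a point.

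The cost is one sentence in section 8, the Table 1 clarification and two degrees of freedom out of roughly 150. No new data, visits or children are needed.

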### **Medische achtergrond van uw kind**

11. Gebruikt uw kind momenteel medicatie voor ADHD?

☐ ja      ☐ nee

12. Wordt uw kind momenteel psychiatrisch of psychotherapeutisch behandeld voor ADHD?

☐ ja      ☐ nee

13. Ontvangt u momenteel ouderbegeleiding vanuit de eigen GGZ-instelling?

☐ ja      ☐ nee

14. Ontvangt u momenteel psycho-educatie vanuit de eigen GGZ-instelling?

☐ ja      ☐ nee

**C. BRIEF Parent version, Subscale Planning and Organizing, version 01**

Het is de bedoeling dat u bij onderstaande beschrijvingen (middels nooit, soms, vaak) aangeeft in welke mate deze van toepassing is op uw kind zoals hij/zij nu is of in de afgelopen twee weken is geweest.

|                                                                                                                                                | Nooit                 | Soms                  | Vaak                  |
|------------------------------------------------------------------------------------------------------------------------------------------------|-----------------------|-----------------------|-----------------------|
| 1. Brengt huiswerk, opgaven, spulletjes etc. niet mee naar huis                                                                                |  |  |  |
| 2. Heeft goede ideeën, maar krijgt ze niet op papier                                                                                           |  |  |  |
| 3. Legt geen link tussen het doen van huiswerk en het behalen van cijfers (als uw kind nooit huiswerk heeft, kruis hier het vakje "nooit" aan) |  |  |  |
| 4. Vergeet het huiswerk in te leveren, ook als het af is (als uw kind nooit huiswerk heeft, kruis hier het vakje "nooit" aan)                  |  |  |  |
| 5. Raakt verstrikt in details en verliest het algemene overzicht                                                                               |  |  |  |
| 6. Heeft goede ideeën, maar kan ze niet uitvoeren (geen doorzettingsvermogen)                                                                  |  |  |  |
| 7. Raakt overweldigd door grote opgaven                                                                                                        |  |  |  |
| 8. Onderschat de tijd die nodig is om taken af te maken                                                                                        |  |  |  |
| 9. Begint pas op het laatste moment aan opdrachten of karweitjes                                                                               |  |  |  |
| 10. Denkt niet vooruit bij huiswerkopdrachten (als uw kind nooit huiswerk heeft, kruis hier het vakje "nooit" aan)                             |  |  |  |
| 11. Geschreven werk ziet er slordig uit                                                                                                        |  |  |  |
| 12. Heeft moeite dingen te doen die nodig zijn om doelen te bereiken (geld sparen voor iets speciaals, leren voor een goed cijfer)             |  |  |  |

### ***D. Time management self constructed questionnaire, version 01***

Het is de bedoeling dat u bij onderstaande beschrijvingen (middels een cijfer van 1 tot en met 10) aangeeft in welke mate deze van toepassing is op uw kind zoals hij/zij nu is of in de afgelopen twee weken is geweest.

|                                                                                                                                                                                                             | Helemaal
niet waar |                       |                       |                       |                       | Helemaal
waar      |                       |                       |                       |                       |
|-------------------------------------------------------------------------------------------------------------------------------------------------------------------------------------------------------------|-----------------------|-----------------------|-----------------------|-----------------------|-----------------------|-----------------------|-----------------------|-----------------------|-----------------------|-----------------------|
|                                                                                                                                                                                                             | 1                     | 2                     | 3                     | 4                     | 5                     | 6                     | 7                     | 8                     | 9                     | 10                    |
| 1. Mijn kind kan een korte taak afmaken, binnen de door u bepaalde tijd                                                                                                                                     |  |  |  |  |  |  |  |  |  |  |
| 2. Mijn kind kan bedenken hoeveel tijd nodig is om een klusje voor een deadline af te maken                                                                                                                 |  |  |  |  |  |  |  |  |  |  |
| 3. Mijn kind kan zonder hulp binnen een bepaalde tijd het ochtendritueel doorlopen                                                                                                                          |  |  |  |  |  |  |  |  |  |  |
| 4. Mijn kind kan zonder hulp binnen een redelijke tijd dagelijkse activiteiten uitvoeren                                                                                                                    |  |  |  |  |  |  |  |  |  |  |
| 5. Mijn kind kan zijn/haar huiswerkplanning aanpassen ten behoeve van andere activiteiten (bijvoorbeeld vroeger beginnen op een avond dat hij/zij gaat sporten of naar muziekles gaat)                      |  |  |  |  |  |  |  |  |  |  |
| 6. Mijn kind kan op tijd met een lange termijnproject beginnen. Zodat de kans op tijdnood kleiner wordt                                                                                                     |  |  |  |  |  |  |  |  |  |  |
| 7. Mijn kind heeft huiswerk meestal voor bedtijd af                                                                                                                                                         |  |  |  |  |  |  |  |  |  |  |
| 8. Mijn kind neemt goede beslissingen over prioriteiten als de tijd beperkt is (gaat bijvoorbeeld vanuit school direct naar huis om een lange termijnopdracht af te maken en gaat niet met vrienden spelen) |  |  |  |  |  |  |  |  |  |  |
| 9. Mijn kind kan een lange termijnproject over verschillende dagen uitsmeren                                                                                                                                |  |  |  |  |  |  |  |  |  |  |
| 10. Mijn kind raffelt op het laatste moment klusjes en/of taken af                                                                                                                                          |  |  |  |  |  |  |  |  |  |  |
| 11. Mijn kind kijkt uit zichzelf regelmatig op de klok (of zijn/haar horloge)                                                                                                                               |  |  |  |  |  |  |  |  |  |  |

**E. “It is about time” Questionnaire, Parent version, Revision 17.02.1998**

Het is de bedoeling dat u bij onderstaande beschrijvingen (middels zelden, soms, meestal, bijna altijd) aangeeft in welke mate deze van toepassing is op uw kind zoals hij/zij nu is of in de afgelopen twee weken is geweest.

|                                                                                                                                                                                               | Zelden                | Soms                  | Meestal               | Bijna altijd          |
|-----------------------------------------------------------------------------------------------------------------------------------------------------------------------------------------------|-----------------------|-----------------------|-----------------------|-----------------------|
| U geeft uw kind een taak of opdracht die hij/zij binnen een bepaalde tijdslimiet moet uitvoeren. Hoe groot is de kans dat hij/zij erin slaagt om die taak af te ronden binnen de tijdslimiet? |  |  |  |  |
| Hoe vaak praat uw kind over wat hij/zij heeft gedaan in het verleden in vergelijking met andere kinderen van dezelfde leeftijd?                                                               |  |  |  |  |
| Hoe vaak stelt uw kind vragen over zijn/haar verleden?                                                                                                                                        |  |  |  |  |
| Hoe vaak praat uw kind over toekomstige of naderende gebeurtenissen waarbij hij/zij betrokken zal zijn?                                                                                       |  |  |  |  |
| Hoe vaak stelt uw kind vragen over dingen die zullen gebeuren in de toekomst?                                                                                                                 |  |  |  |  |
| Hoe vaak gebruikt uw kind een klok of horloge om na te gaan hoeveel tijd hij/zij nog heeft om iets te doen?                                                                                   |  |  |  |  |
| Hoe vaak plant uw kind dingen met anderen die zullen plaatsvinden op een latere datum of een later tijdstip?                                                                                  |  |  |  |  |
| Uw kind moet een deadline respecteren. Hoe groot is de kans dat hij/zij klaar of voorbereid is tegen die deadline?                                                                            |  |  |  |  |
| Het is bedtijd en uw kind ligt in bed. Hoe vaak praat of denkt uw kind na over wat hij/zij die dag heeft meegemaakt?                                                                          |  |  |  |  |
| Het is bedtijd. Hoe vaak praat of denkt uw kind na over wat hij/zij de volgende dag zal doen?                                                                                                 |  |  |  |  |
| Hoe vaak vindt uw kind het moeilijk om te wachten tot hij/zij iets mag doen wat hij/zij liefst meteen al zou doen?                                                                            |  |  |  |  |
| Hoe vaak lijkt uw kind terug te denken in de tijd of kennis uit het verleden te gebruiken voor hij/zij reageert in een situatie?                                                              |  |  |  |  |
| Hoe vaak lijkt uw kind vooruit te denken of vooruitziend te zijn voor hij/zij reageert op een situatie?                                                                                       |  |  |  |  |

|                                                                                                                                                                                                               | Zelden                | Soms                  | Meestal               | Bijna altijd          |
|---------------------------------------------------------------------------------------------------------------------------------------------------------------------------------------------------------------|-----------------------|-----------------------|-----------------------|-----------------------|
| Hoe vaak lijkt uw kind vooraf te plannen wat hij/zij wil doen in vergelijking met andere kinderen van dezelfde leeftijd?                                                                                      |  |  |  |  |
| Hoe vaak heeft uw kind zijn/haar huiswerk op tijd klaar?                                                                                                                                                      |  |  |  |  |
| Hoe vaak is uw kind 's ochtends op schooldagen tijdig klaar om te vertrekken?                                                                                                                                 |  |  |  |  |
| Hoe vaak denkt uw kind na over de toekomstige gevolgen van zijn/haar handelingen voor zichzelf?                                                                                                               |  |  |  |  |
| Hoe vaak denkt uw kind na over de toekomstige gevolgen van zijn/haar handelingen voor anderen?                                                                                                                |  |  |  |  |
| Uw kind werkt aan een taak. Hoe vaak lijkt hij/zij de taak te kunnen afronden binnen de toegestane tijd?                                                                                                      |  |  |  |  |
| Uw kind gaat ergens naartoe om iets te doen (bv. hij/zij gaat buiten spelen) en u zegt hem/haar dat hij/zij op een bepaald tijdstip terug thuis moet zijn. Hoe groot is de kans dat hij/zij op tijd terug is? |  |  |  |  |
| Uw kind heeft een taak. Hoe vaak stelt hij/zij die taak uit?                                                                                                                                                  |  |  |  |  |
| Uw kind belooft iets voor u te doen op een later tijdstip van de dag. Hoe groot is de kans dat hij/zij dat nog uit zichzelf weet zonder dat u hem/haar eraan moet herinneren?                                 |  |  |  |  |
| U belooft uw kind een beloning in de verre toekomst wanneer hij/zij nu meteen iets voor u doet. Hoe groot is de kans dat hij/zij die taak meteen doet?                                                        |  |  |  |  |

**Uw kind moet over een paar weken een schooltaak (bv. een boekbespreking of wetenschappelijk werk) inleveren. Hoelang op voorhand begint hij/zij zich voor te bereiden op die deadline?**

- |                                                                                     |                       |
|-------------------------------------------------------------------------------------|-----------------------|
| a) Hij/zij begint er meteen aan te werken                                           |  |
| b) Hij/zij wacht tot een week voor de deadline en begint er dan aan te werken       |  |
| c) Hij/zij wacht tot een paar dagen voor de deadline en begint er dan aan te werken |  |
| d) Hij/zij wacht tot een dag voor de deadline en begint er dan aan te werken        |  |
| e) Hij/zij wacht tot de dag van de deadline en begint er dan aan te werken.         |  |
| f) Hij/zij bereidt zich helemaal niet voor                                          |  |

**Hoe goed is het tijdsgevoel van uw kind ontwikkeld, over het algemeen en in vergelijking met andere kinderen van zijn/haar leeftijd?**

- |                             |                       |
|-----------------------------|-----------------------|
| a) Slecht                   |  |
| b) Onder het gemiddelde     |  |
| c) Gemiddeld                |  |
| d) Boven het gemiddelde     |  |
| e) Ver boven het gemiddelde |  |

